### Study Procedures

All subjects contacted for the study will be screened over the telephone by trained master’s level research assistants. Those who seem eligible will be invited for two in-person assessments. The screening visit will include a diagnostic interview for Axis I and II disorders (SCID-I and SCID-II) and a semi-structured interview to assess the subject’s SAD and depression symptoms and insight into SAD-related beliefs (LSAS, SPIN, QIDS, BAPS). The diagnostic interviews will be conducted by trained [doctoral-level] independent raters who are blind to treatment conditions. Patients who are eligible will be randomized either to the CT plus enhanced BEs group or to the Standard CT group and invited for a baseline visit to complete a self-reported questionnaire. The outcome measures will be assessed by the independent raters upon the termination of treatment and after 6months. The study protocol adheres to the Standard Protocol Items: Recommendations for Interventional Trials (SPIRIT) checklist (Additional file 1).

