### Randomization

We will use two levels of randomization. Firstly, therapists are randomized to either CT + BEs or Standard CT as described above. Secondly, participants will be randomly assigned to a therapist of one of the two treatment conditions. The random allocation sequence will be generated by a randomization program [19]. Allocation to treatment of the patients is concealed from investigators and patients. The random allocation schedule will be drawn up and administered by a psychologist from another department of the university who is not involved in the further study process. After meeting the inclusion criteria, the participant is allocated by this psychologist to a therapist of one of the treatment conditions. The investigators and therapists are informed about the allocation.

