### Additional Assessments

For competence and adherence ratings, three videotapes will be selected: one from the initial stage (session 1, deriving the model) and two from the second stage (random selection from session 5–12). Session 1 is selected to cover general competencies such as guided discovery, whereas sessions from the second stage of treatment onwards are expected to refer to specific competencies (conducting BEs vs. cognitive restructuring). Competence and adherence will be rated by two independent, masked, and trained raters using the Cognitive Therapy Adherence Scale for Social Phobia (CTAS-SP) [18] the Cognitive Therapy Competence Scale for Social Phobia (CTCS-SP) [30]. The CTAS-SP comprises 17 items related to the specific interventions of CT, as described in the manual by Stangier et al. [17]. In the SOPHONET trial [6], a good interrater reliability (ICC = 0.87) was observed. Retest reliability was rtt = 0.90 for the total score and rtt = 0.28–1.0 for the individual items. Internal consistency was high (α = 0.99). Similarly, the psychometric properties of the 16-item CTCS-SP were good, with an interrater reliability of ICC = 0.81, retest reliability of rtt = 0.92, and an internal consistency of α = 0.97.

To assess the therapeutic relationship, the Helping Alliance Questionnaire (HAQ, patient and therapist version) will be used [31]. Both questionnaires will be administered at pre-treatment. The mean scores of the therapist and patient versions will be used to predict the outcomes.

Allegiance is assessed after the training and one pilot-therapy by the therapist version of the Reaction to Treatment Questionnaire developed by Holt & Heimberg [32]. For the purpose of the present study, two further items have been added to the scale referring to outcome expectations about specific intervention (BEs and cognitive restructuring).

As a predictor of treatment success, a 12-item version of the learning style inventory (Kolb LSI) will be administered at pre-treatment [33]. Based on previous treatment study results [34], it is hypothesized that the outcome of participants in the BE intervention will significantly predict an active experimentation learning style, whereas for participants in the standard CT (cognitive restructuring), the preferred learning style is predicted to be an abstract conceptualization learning style.

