### Statistical Analyses

Data will be analyzed with the SPSS statistical software package. All statistical analyses will be conducted on the intent-to-treat (ITT) sample and completer sample. Patients allocated to treatments will be classified as drop-outs if they miss more than 25% of the sessions. In the ITT analyses of treatment response, drop-outs will be considered as failures. In ITT analyses of dimensional measures, missing data will be replaced using the last observation carried forward approach for missing intervention- and post-assessments or follow-up observations. Analyses of the primary outcome measure (CGI-I), a categorical variable, will be conducted using χ^2^ or Fisher's exact tests. Dimensional measures will be submitted to analyses of covariance (ANCOVAs) in which pre-treatment scores will be controlled for. ANCOVAS will be performed separately for the post-treatment and 6-month follow-up assessments. Significance levels will be set at *p* < 0.05, two-tailed. Predictor analysis will be calculated by using logistic regression analysis with CGI-I as the dependent variable; independent variables are competencies, adherence, allegiance, and therapist-rated therapeutic relationships (therapist predictors), as well as patients’ preferred learning style at pre-treatment, changes in insight in SAD-related beliefs and cognitions, and patient-rated therapeutic relationships (patient predictors). Differences between treatments in the outcome predictions will be analyzed, with treatment interactions for each predictor. To test for possible therapist differences, a preliminary analysis of covariance will be conducted. As recommended, significance level in this case will be set at *p* < .30 [37]. If the effect is significant, a multilevel analysis using a mixed-model design is planned to include therapists as a random term [38]. A final analysis will be run to compare the pattern of results from both strategies of analysis taking possible therapist effects into consideration.

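### Baseline self-reports not listed at screening can be completed after allocation, which exposes the learning style moderator and probably the BDI-II baseline

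*Protocol article*

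**What the plan says.** Study Procedures describes two in-person assessments. The screening visit holds the diagnostic interview and the assessment of "SAD and depression symptoms and insight into SAD-related beliefs (LSAS, SPIN, QIDS, BAPS". The next step is allocation: "Patients who are eligible will be randomized either to the CT plus enhanced BEs group or to the Standard CT group", and the same sentence continues that they are "invited for a baseline visit to complete a self-reported questionnaire". The instruments in that questionnaire are not named.

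The Randomization section gives the same trigger: "After meeting the inclusion criteria, the participant is allocated by this psychologist to a therapist of one of the treatment conditions". On who knows the result it says two things: "Allocation to treatment of the patients is concealed from investigators and patients" and, at the end of the section, "The investigators and therapists are informed about the allocation".

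On use of the baselines, Statistical Analyses says: "Dimensional measures will be submitted to analyses of covariance (ANCOVAs) in which pre-treatment scores will be controlled for". Under Additional Assessments, "a 12-item version of the learning style inventory (Kolb LSI) will be administered at pre-treatment". Statistical Analyses then enters learning style in a logistic regression for CGI-I response, with a treatment interaction for each predictor. Outcome Measures lists the BDI-II total as a change-from-baseline measure.

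**The concern.** A baseline covariate or moderator is protected by randomisation only if allocation cannot influence it. The usual guarantee is to measure it first. Here the written order is the reverse for whatever is collected at the baseline visit.

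Three things are at stake.

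- **Learning style.** Additional Assessments links active experimentation to the behavioural-experiment arm and abstract conceptualisation to standard CT. A patient who knows the assigned treatment could describe a style that fits it. The treatment-by-style interaction under Hypothesis 4 would then be tested on a moderator that the treatment assignment had partly shaped.
- **BDI-II.** If the pre-treatment score is an ANCOVA covariate and allocation shifts it in one arm, part of that shift is carried into the estimated treatment difference.
- **Missing baselines.** A patient who is randomised but lost before the visit has no value for these instruments. Last observation carried forward cannot supply one, because no earlier observation exists.

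**Working it through.** No figure in the plan is at issue, so the check sets the sections side by side and then illustrates the mechanism.

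**Step 1: order.** Study Procedures runs screening, randomisation, baseline visit. Randomization makes the trigger the inclusion criteria, which are settled at screening. No section requires the baseline self-report to be finished before allocation. The two sections agree with each other.

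**Step 2: which measures are exposed.**

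| Measure | Timing in the text | Exposed? |
|---|---|---|
| CGI-I response (primary) | post-treatment; χ² or Fisher test, no baseline covariate | no |
| LSAS, SPIN, QIDS, insight scale | listed at screening | no |
| Learning style inventory | pre-treatment, not listed at screening | probably |
| BDI-II | baseline value needed, not listed at screening | probably |
| SCQ | each session; no pre-treatment visit given | not assigned to this visit |
| Alliance questionnaire (patient, therapist) | pre-treatment, but rates an assigned therapist | after assignment by its nature |

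The abstract names the LSAS as the primary measure. Its baseline is taken at screening, so the conclusion on the primary outcome is the same on either reading.

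**Step 3: can the patient know the arm?** Therapists are themselves randomised to one condition and trained separately, and patients are assigned to a therapist. Knowing the therapist can therefore reveal the arm. Investigators and therapists are told. Patients are said to be concealed from, but no end point is given.

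**Step 4: mechanism for an ANCOVA covariate (BDI-II only).** Let the follow-up score depend on the true pre-allocation level with slope *b*. Let allocation shift the reported baseline in one arm by *s* (both in SD units). The ANCOVA treatment estimate is then biased by −*b* × *s*. The document gives neither *b* nor *s*, so these values are assumptions:

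- *b* = 0.3, *s* = 0.1: −0.3 × 0.1 = −0.03 SD
- *b* = 0.5, *s* = 0.2: −0.5 × 0.2 = −0.10 SD
- *b* = 0.7, *s* = 0.3: −0.7 × 0.3 = −0.21 SD

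A simulation with 30 per arm and no true effect agrees:

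| *b* | *s* | Mean bias (SD) | Type I error at nominal 0.05 |
|---|---|---|---|
| 0.5 | 0 | 0.00 | 0.05 |
| 0.5 | 0.2 | −0.10 | 0.07 |
| 0.7 | 0.3 | −0.22 | 0.21 |

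This shows the direction and that the bias vanishes when the covariate precedes allocation. It does not estimate the bias in this trial. The formula also does not apply to learning style, which is a moderator in a logistic regression and not an ANCOVA covariate.

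**The case against.** The strongest reply is that self-report can be biased only if the patient knows the arm, and the Randomization section says that allocation is concealed from patients and does not list them among those informed. Both arms are active CT with the same contact hours, and the protocol takes steps against devaluing the control, so a large shift before any session is not obvious. This stands as a reason for restraint about size. It does not remove the risk. The same sentence also names the investigators as concealed from, and the section then says that they are informed, so concealment there plainly ends at some point. For patients that point is not stated.

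A second reply is that the list of exposed instruments is inference. The questionnaire is unnamed, the schedule figure is not shown, and Outcome Measures mentions the BDI-II in a sentence about independent ratings. This also stands, which is why the list is given as probable.

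A third is that the sentence in Study Procedures might not be meant as a sequence. The trigger in the Randomization section points the other way, and if another order is intended the sentence still needs correcting.

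A reader might go further and infer that the SAD outcomes are biased, or that the bias is some percentage of the planned d = 0.60. The documents support neither. The LSAS and SPIN baselines precede randomisation, the primary test uses no baseline, and the planning effect was not set for the BDI-II. Nor does the text show that the first SCQ belongs to this visit. If it is taken at the first session, it follows allocation whatever the order of the visits.

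**Conclusion.** The point holds in a limited form. The written sequence allows baseline self-reports not listed at screening to be completed after allocation, and nothing in the text ensures that patients are unaware of their arm when they complete them. The main exposure is the learning style interaction, followed by the BDI-II comparison if its pre-treatment score is the covariate. A smaller issue is that patients lost between randomisation and the visit would lack these baselines.

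The primary CGI-I result and the LSAS, SPIN, QIDS and insight-scale baselines are untouched. The size of any bias cannot be derived from the document; the 0.03 to 0.21 SD range above rests wholly on assumed slopes and shifts. The verdict assumes that the learning style inventory and BDI-II are collected at the baseline visit, and the schedule figure could confirm or refute this.

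**What to change.** Reorder Study Procedures so that eligible patients complete the baseline self-report and the independent psychologist releases the allocation only afterwards. The visit should include the BDI-II and the learning style inventory, plus one SCQ if a pre-treatment SCQ score is to be used. The alliance questionnaire stays after assignment, because it rates an assigned therapist. The Randomization section should make completion of these forms a condition of allocation alongside the inclusion criteria.

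The cost is an amendment that swaps two steps, with no extra visit or staff. The downside is that a few patients will complete forms and then not be randomised.

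For patients already enrolled, report that these baselines were taken after allocation. As a sensitivity analysis, repeat the BDI-II comparison without the BDI-II baseline as covariate, or with the pre-randomisation QIDS score in its place. Excluding patients with post-allocation baselines is not an option, since under the written order that would be everyone enrolled so far.

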### Recruitment

Patients will be recruited through the outpatient unit at Goethe University Frankfurt (Zentrum für Psychotherapie), and by mental health professionals, support groups, patient organizations, flyers at local sites (e.g., primary care), and advertisements in mass media and newspapers.

### Selection of Patients

Patients will be included if they meet the following criteria:
primary diagnosis of SAD (German SKID modified for DSM-5)age 18–70 yearsno concurrent psychopharmacological or psychotherapeutic treatmentwritten informed consent must be available before study participation

Patients presenting with any of the following criteria will not be included in the study:
acute suicidalityactive substance abuse or dependence within the past 3 monthssevere depressionpsychotic disorderbipolar disorderborderline personality disorderorganic mental disorder and/or severe medical conditions

Patients may be withdrawn from the study for the following reasons:
on request of the patient (withdrawal of the patient’s consent)if continuation of the study would be detrimental to the subject’s well-beingoccurrence of exclusion criteria

The investigator will decide whether to withdraw patients from the study in cases of 2) and 3). There are no specific plans to promote participant retention. Participants who discontinue will be asked to complete all assessments.

### Treatments

In the study, two conditions, CT plus enhanced BEs vs. standard CT, are compared; these use different interventions in the middle stage of treatment to achieve a change in SAD-related cognitions:
behavioral experimentstraditional (verbal) methods of cognitive restructuring.

CT based upon the Clark & Wells model pursues two primary goals:
to reverse the processes that maintain SAD (self-focused attention, distorted images of the social self, and safety behaviors), andto disconfirm dysfunctional beliefs (using BE, imagery rescripting, and cognitive restructuring).

As described in detail in the revised manual [16], the treatment comprises the following interventions:
Stage 1 (sessions 1–3): deriving an individual cognitive model, experiential exercises to avoid self-focused attention and safety behaviors, providing video feedback, and enhancing attention training;Stage 2 (sessions 4–13): BEs (in-session and homework) to test dysfunctional beliefs, and imagery rescripting to modify maladaptive beliefs linked to recurrent negative imagery;Stage 3 (14–17): termination of treatment (blueprint of techniques helpful for relapse prevention) and booster session.

To implement BEs, prolonged sessions are required to prepare the experiment, including defining the expectations to be tested, outlining the behaviors to be enacted in the experiment, and choosing an appropriate situation outside the therapy room. Thus, 2 × 50 min will be scheduled as the standard duration of the session.

Furthermore, guided discovery and standard CT discussion techniques are used in stage 2 to support the reflection of BEs consequences. However, no automatic thoughts records are used, and verbal techniques of cognitive restructuring are embedded in the planning of BEs and the analysis of the results. In contrast to standard CT, therapists will use the Social Cognitions Questionnaire (SCQ) on a weekly basis to determine the focus of the therapy.

As in standard CT, neither exposure based on a rational habituation nor formal social skills training is used.

Standard CT comprises similar elements in the first and third stage of therapy; however, in the middle stage (stage 2), discussion techniques of challenging dysfunctional beliefs are used instead of BE. The techniques are described in detail in the previous manual [17] and include Socratic dialogue, the downward arrow technique, the prejudice technique, the life chart technique, positive data log, automatic thoughts protocol, and the pie chart technique. Dysfunctional beliefs associated with early experiences are identified and discussed. Homework mainly focuses on automatic thoughts and the practice of Socratic dialogue.

In standard CT, therapists are not encouraged to use BEs. Neither exposure based on a habituation rational nor formal social skills training is used.

To equalize therapists’ contact time and treatment dose, both treatments comprise the same amount of contact hours. In line with short-time-therapy in Germany, 25 units of 50-min duration are provided. In CT + BEs, up to eight sessions last 100 min due to the implementation of BEs. Standard CT includes one session of 100-min duration. Thus, the total number of sessions differs (17 vs. 25). The length of both treatments, however, is 6 months, since booster sessions are conducted (4-week interval) in the end of CT + BEs as prescribed in the manual.

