In addition, to ensure equal allegiance, we also try to control for differences between conditions in adherence. Both groups of therapists receive detailed manuals [16], extended training, and continuous supervision. An additional adherence check will be established by the analysis of videotaped sessions [11].

A focus of the training in the experimental conditions is to overcome barriers, that have also been found in the implementation of exposure into practice. One of the reasons for the underutilization of in vivo exposure in previous studies could be a lack of flexibility in terms of time and location, which is necessary to approach the anxiety provoking situation and implement exposure and response prevention until habituation [45]. Similar to in vivo exposure [46], the presence of the therapist in situ is required to overcome avoidance, identify and drop safety behaviors, ensure that the critical behavior is performed, model the critical behavior to allow for observational experiments, instruct the patient to externalize attention and accurately assess other people’s reactions. However, the preference for 50-min sessions in the German health care setting may have limited the conditions to leave the therapy room and guide BEs in situ. Thus, to support flexibility we plan double sessions as obligatory part of CT + BEs. The contact time and use of prolonged sessions will be assessed by the therapist after every session.

In addition, specific competencies are needed to conduct BEs and build up motivation for approaching anxiety-provoking situations. Therefore, therapists receive detailed instructions, e.g., how to operationalize key beliefs into concrete expectations related to specific situations, how to encourage the patient to approach this situation, to instruct the patient to drop safety behaviors and self-attention, to encourage the patient to enact critical behavior related to feared outcomes (e.g., blushing), and to review the actual outcome in relationship to expected outcome. An additional part of the training will be a one pilot-therapy of the first patient to consolidate the competence and counteract negative expectations. For further support, we provide continuous supervision by the senior investigator.

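### The printed session counts do not match the stated equal dose of 25 units per arm: standard CT adds up to 26, and CT + BEs reaches 25 only with exactly eight double sessions

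*Protocol article*

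**What the plan says.** The Treatments section states the dose for both arms directly: "both treatments comprise the same amount of contact hours", and "25 units of 50-min duration are provided". It gives the purpose as equalising contact time and dose.

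It then breaks this dose into sessions. For the experimental arm, "In CT + BEs, up to eight sessions last 100 min due to the implementation of BEs". For the control arm and the resulting totals, "Standard CT includes one session of 100-min duration. Thus, the total number of sessions differs (17 vs. 25"). The totals are 17 sessions for CT + BEs and 25 for standard CT.

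Two other statements bear on the experimental arm:

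- Earlier in Treatments, the stage outline numbers the sessions 1–3, 4–13 and 14–17. The paragraph on prolonged sessions for BEs says that 2 × 50 min "will be scheduled as the standard duration of the session".
- The Discussion says "we plan double sessions as obligatory part of CT + BEs". It adds that therapists will record contact time and use of prolonged sessions after every session.

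**The concern.** The total dose, the number of sessions and the number of double sessions are all printed for each arm, so they can be checked against each other, and they do not agree.

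This matters because the Discussion describes the two arms as differing in one component, the behavioural experiment. That reading needs contact time to be equal, and equal contact time is the protection the plan offers. Session length is also part of the trial's rationale: the Background suggests short sessions as one reason for weaker results in the German and Swedish trials, and the Hypotheses section lists double-hour sessions among the measures meant to improve CT. A reader should be able to tell what each arm is scheduled to receive.

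The number of sessions has a second use. Under Statistical Analyses, a patient who misses more than 25% of sessions is a drop-out, and drop-outs count as failures in the ITT analysis of response. The scheduled count is therefore a denominator in the primary analysis, and it is worth checking whether the inconsistency reaches that far.

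**Working it through.** **Inputs** (all from Treatments): 25 units of 50 min per arm; CT + BEs 17 sessions, at most 8 double; standard CT 25 sessions, 1 double; stage 2 is sessions 4–13.

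**Formula.** With s sessions, d of them double, units = (s − d) + 2d = s + d, and minutes = 50 × units. The stated dose is 25 × 50 = 1,250 min.

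**CT + BEs, the plan's figure reproduced.** The stages give 3 + 10 + 4 = 17 sessions, which agrees with the printed count. With d = 8, units = 9 + 16 = 25. The stated dose is met exactly, but only at the upper limit.

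**CT + BEs below the limit.** The text says "up to eight sessions last 100 min due to the implementation of BEs" and gives no minimum.

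- Holding 17 sessions, units = 17 + d. Seven doubles give 24 units, one short.
- Holding 25 units, sessions = 25 − d. Seven doubles give 18 sessions, not 17.

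So for any d below 8, either the 25 units or the 17 sessions must give way.

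**Standard CT.** With s = 25 and d = 1, units = 24 + 2 = 26, or 1,300 min. The excess over the stated dose is 1 unit, 50 min, and 50 / 1,250 = 4%. Arithmetically, 25 units would arise from 24 sessions with one double (23 + 2) or from 25 sessions with none. These only show where the sum fails; they are not proposals.

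**Standard session length.** Stage 2 has 13 − 4 + 1 = 10 sessions. If the 2 × 50 min standard applied to all ten, units = 17 + 10 = 27 and there would be ten doubles, against a cap of eight.

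**Drop-out cut-off** (more than 25% of sessions missed).

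| Arm and session count | 25% of count | Missed sessions that make a drop-out |
|---|---|---|
| Standard CT, 25 | 6.25 | 7 |
| Standard CT, 24 | 6.00 | 7 |
| CT + BEs, 17 | 4.25 | 5 |
| CT + BEs, 18 | 4.50 | 5 |

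The one-unit discrepancy leaves the standard CT cut-off at seven.

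**The case against.** The strongest reply is that the text fixes the dose itself at 25 units for both arms, and the session counts are only derived from it. CT + BEs reproduces 25 at its planned maximum. Only the standard CT count is off, by one, which looks like a counting slip. The extra unit would go to the control arm, so it could not by itself create an apparent benefit of BEs. All of this stands, and it limits the size of the point.

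A reader might go further and infer that the equal-dose claim is simply false, with large gaps: 17 units against 26 if no CT + BEs session is double (35% less), or 34 against 26 if all 17 are double (31% more). The documents do not support either.

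- **17 units** requires no double sessions, although the Discussion makes them obligatory, and it discards the stated 25 units.
- **34 units** is excluded by the cap of eight. The sentence on standard duration closes a paragraph about implementing BEs and can be read as covering BE sessions only.

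Nor does the Discussion's statement conflict with the cap: it requires the arm to contain double sessions without saying how many.

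A reader might also infer that the discrepancy changes who counts as a failure in the primary analysis. For the certain error it does not, as the cut-offs show.

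Finally, it can be said that a table of delivered minutes is ordinary reporting content. That is fair, and its absence is not the finding. The finding is that the printed figures contradict each other.

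**Conclusion.** The point holds as an internal inconsistency in the treatment-dose figures. The certain part is one 50-minute unit: standard CT adds up to 1,300 min against the stated 1,250 (4%), in favour of the control arm. This rests only on the printed 25 sessions and one double session.

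The second part is looseness whose size the document does not fix. CT + BEs meets 25 units in 17 sessions only at exactly eight doubles, while the wording allows fewer. Whether fewer doubles would mean less contact time or more sessions depends on which printed figure governs, and the text does not say. The standard duration of 2 × 50 min, beside ten stage 2 sessions and a cap of eight, adds to the uncertainty.

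Nothing here shows a large planned dose difference or a bias towards CT + BEs. What it shows is that the equal-contact claim, on which the comparison of the arms relies, is not borne out by the numbers given for it.

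**What to change.** - Reconcile the statements in Treatments (stage outline and standard session duration, session counts, double sessions, units) with the statement on double sessions in the Discussion, so that sessions, double sessions and 50-minute units add up in each arm. Which schedule is intended is for the sponsor to decide.
- Restate the claim of equal contact hours to match the reconciled figures.
- Report delivered contact minutes by arm, using the contact time therapists already record after every session, and claim equal dose only if those data support it.

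The cost is a few lines of wording and one descriptive table. No new data collection is needed, and the sample size and primary test are unaffected.
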